## 10.0 Safety reporting

The following definitions are in accordance with ICH-GCP.

**Adverse Event (AE):** Any untoward medical occurrence in a clinical trial participant which does not necessarily have a causal relationship with their treatment. An AE can therefore be any unfavourable and unintended sign (including abnormal laboratory finding), symptom, or disease.

An adverse event that causes, or has the potential to cause, unexpected or unwanted effects involving the safety of patients, users or other persons can include:

- A patient, carer or professional is injured as a result of a medical device failure or misuse
- A patient's treatment is interrupted or compromised by medical device failure
- A patient's health deteriorates due to medical device failure

An adverse event in medical devices may arise due to:

- Shortcomings in the manufacture or design of the device itself
- Inadequate instructions for use
- Inadequate servicing or maintenance
- Locally initiated modifications or adjustments
- Inappropriate user practices (which could arise from inadequate training)
- The environment in which the device is used or stored

Adverse events should be reported to the WCTU to identify the rate at which they occur and the severity of outcome.

Adverse events may include any noxious and unintended response in a clinical trial participant to whom an investigational medicinal device has been administered, which is related to any intensity level administered.

An adverse event with a medical device means that a causal relationship between a medical device and is at least a reasonable possibility, i.e. the relationship cannot be ruled out.

The expected adverse reactions for Microstim 2 (v2) are tabulated below:

- |                                                                                                                                                                |
|----------------------------------------------------------------------------------------------------------------------------------------------------------------|
| 

• Post-NMES muscle soreness

• Erythema following NMES

• Rash on skin in reaction to electrodes

 |
|----------------------------------------------------------------------------------------------------------------------------------------------------------------|

**Serious Adverse Event (SAE):** Any adverse event that:

- Results in death
- Is life-threatening\*
- Required hospitalisation or prolongation of existing hospitalisation\*\*
- Results in persistent or significant disability or incapacity
- Consists of a congenital anomaly or birth defect
- Other medically important condition \*\*\*

\* Note: The term "life-threatening" in the definition of serious refers to an event in which the patient was at risk of death at the time of the event; it does not refer to an event which hypothetically might have caused death if it were more severe.

\*\* Note: Hospitalisation is defined as an inpatient admission, regardless of the length of stay, even if the hospitalisation is a precautionary measure, for continued observation. Pre-planned hospitalisation e.g. for pre-existing conditions which have not worsened or elective procedures does not constitute an adverse event.

\*\*\* Note: other events that may not result in death, are not life-threatening, or do not require hospitalisation may be considered as a serious adverse event when, based upon appropriate medical judgement, the event may jeopardise the participant and may require medical or surgical intervention to prevent one of the outcomes listed above.

Adverse events (AE) and AIs should be graded using the NCI Common Terminology Criteria for Adverse Events (CTCAE) Version 3.0. The toxicity grades should be recorded on the CRF.

A SAE form is not considered as complete unless the following details are provided:

- Full participant trial number
- An adverse event/reaction
- A completed assessment of the seriousness, causality and expectedness as performed by the Principal Investigator or another appropriately qualified clinician registered on the delegation log

If any of these details are missing, you will be contacted and the information must be provided as soon as it becomes available.

## 10.1 Pregnancy reporting whilst participating in the NMES trial

Pregnancy, occurring whilst participating in the NMES trial, although not considered an SAE, must be notified to the WCTU within the same timelines as an SAE. In the event of a pregnancy in a trial participant, the WCTU must be contacted immediately to request a Pregnancy Report Form. The Pregnancy Report Form should be completed and returned to the WCTU to capture all the relevant information required for the expedited reporting of these events. The outcome of a pregnancy should be followed up carefully and any abnormal outcome of the mother or the foetus should be reported.

## 10.2 Exceptions

For the purposes of this trial the following SAEs do not require immediate reporting.

- Death or disability due to disease progression
- Hospitalisation for chemotoxicities, e.g neutropenia, infection, nausea
- Toxicities related to palliative radiotherapy

Instead, these should be completed on the relevant CRF page and forwarded to the WCTU in the normal timeframes for CRFs (i.e. within two weeks of completion).

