### 10.3 Centre responsibilities

All SAEs must be reported immediately by the PI at the participating centre to the WCTU and the Chief Investigator unless the SAE/SAR is specified as not requiring immediate reporting (see above). All other AEs should be reported on the CRF as usual. The PI should assess the SAE to determine the likely causality with the trial treatment (graded as definitely, probably, possibly, unlikely or not related) and the expectedness (unexpected or expected). A completed SAE form for all events requiring immediate reporting should be faxed to the WCTU and University of Nottingham within 24 hours of knowledge of the event. A separate form must be used to report each event.

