### 10.4 The Wales Cancer Trials Unit responsibilities

Following the initial report all SAEs should be followed up to resolution wherever possible and further information may be requested by the WCTU. The participant will be identified only by trial number, date of birth and initials. The participant's name should not be used on any correspondence.

WCTU has been delegated responsibility for reporting AEs and SAEs to the regulatory authorities (and relevant ethics committees) as follows:

- A list of all AEs (expected and unexpected) will be reported annually to the Main REC and the trial sponsor.
- The WCTU will report a list of all SARs (expected and unexpected) and any other safety recommendations to all PIs every six months throughout the course of the trial. This frequency may be reviewed and amended as necessary.

Once an SAE or AE is received at the WCTU, it will be evaluated by staff at the WCTU and the Chief Investigator (or their delegate) for seriousness, expectedness and causality.

The causality and expectedness assessment given by the PI cannot be overruled by the CI (or their delegate) and in the case of disagreement, both opinions will be provided with the report. SAEs will be handled at the highest level of event categorisation. This ensures that all SAEs will be reported correctly and included into any Annual / Investigator Safety Reports.

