#### 12.2.2 Secondary outcome measures

*Safety of NMES:* toxicities will be assessed according to the NCI Common Terminology Criteria for Adverse Events (NCI CTCAE v3.0). Serious adverse events will be monitored in "real-time".

*Quadriceps muscle strength:* peak torque (kg) measured using a portable Manual Muscle Tester dynamometer (Lafayette Instruments, USA).

*Body composition:* lean tissue mass of the body and thighs (kg) assessed by low-dose dual energy x-ray absorptiometry (DEXA).

*Physical activity level:* mean daily step count assessed by a small, lightweight activPAL™ accelerometer worn on the thigh for one week.

*Response to chemotherapy:* overall objective clinical response categorised using Response Evaluation Criteria In Solid Tumours, documented from patients' medical reports.

*Nutritional intake:* mean daily energy (kJ/d) and protein (g/d) intake estimated from a 3-day food and drink diary.

*Fatigue:* Multidimensional Fatigue Inventory.

*Quality of life:* the EORTC-C30 and the lung cancer specific module LC-13.

*Experience of NMES:* semi-structured interview exploring patient experiences of completing NMES during chemotherapy.

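### Section 10.2 exempts serious events from immediate reporting by a chemotherapy or progression label, not by a judgement on NMES, so a possibly device-related event can reach the trials unit weeks late

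*Protocol*

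**What the plan says.** Section 10.2 of the protocol opens with "For the purposes of this trial the following SAEs do not require immediate reporting" and lists three groups: death or disability from progression, "Hospitalisation for chemotoxicities, e.g neutropenia, infection, nausea", and toxicities of palliative radiotherapy. For these, "these should be completed on the relevant CRF page and forwarded to the WCTU in the normal timeframes for CRFs", which the section gives as two weeks from completion.

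Section 10.3 requires immediate reporting of all SAEs "unless the SAE/SAR is specified as not requiring immediate reporting (see above"). It ties the expedited form to the remainder: "A completed SAE form for all events requiring immediate reporting should be faxed to the WCTU and University of Nottingham within 24 hours", counted from when the site becomes aware. Section 10.0 treats that form as incomplete unless seriousness, causality and expectedness have been assessed.

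Other sections bear on the same events:

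- Section 10.0 describes a device-related event as one where a causal link "is at least a reasonable possibility, i.e. the relationship cannot be ruled out".
- Section 12.2.2, under safety of NMES, says "Serious adverse events will be monitored in 'real-time". The note to the Section 9.6 schedule says SAEs are collected in real time through a dedicated fax number. Neither mentions an exception.
- Section 11.2 has CRFs returned within four weeks of the visit.
- Section 10.3 asks the PI to grade the SAE for causality with the trial treatment on a five-level scale. Section 10.4 has trials unit staff and the Chief Investigator evaluate any SAE or AE received, including for causality.

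**The concern.** The reporting route depends on a prior attribution. Someone at the site decides that an admission is a chemotherapy toxicity, or that a disability is progression, and that decision removes the event from the 24-hour route. Section 10.2 does not ask whether NMES might have contributed, and it gives no rule for an event with more than one plausible cause. The trial is open, so the person applying the label knows the allocation.

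The overlap with device use is close. Section 10.0 lists muscle soreness, erythema and electrode rash as expected device reactions. An infection that starts at irritated skin under an electrode in a neutropenic patient is a hypothetical example of an event that could be filed under the chemotherapy label. Safety of NMES during chemotherapy is the first secondary objective. At stake is how quickly, and with what recorded judgement, a possibly device-related serious event reaches the people responsible for safety.

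**Working it through.** The protocol gives no figure to reproduce. The check sets the sections side by side.

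**1. Are the listed events still SAEs?** Yes. Section 10.2 calls them SAEs and lifts only the immediacy of reporting.

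**2. Does the exemption depend on a judgement about NMES?** No. Its wording turns on attribution to chemotherapy, radiotherapy or progression. Nothing excludes an event in which a relation to NMES is possible.

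**3. Does it reach reactions?** On its face, yes. Section 10.3 words the exception for SAE/SAR. SAR is read here as serious adverse reaction, a term Section 10.3 later uses in full.

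**4. Does an exempt event need the SAE form?** No. Section 10.3 requires the form only for events needing immediate reporting.

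**5. Where is a causality grade a stated condition of a complete record?** On the SAE form (Section 10.0). No matching requirement is stated for the CRF page.

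**6. Is causality still assessed?** Yes. The PI's duty in Section 10.3 is not limited to expedited events, and the central evaluation in Section 10.4 applies to whatever arrives, by either route.

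**7. How late can an exempt event arrive?** The three limits start from different points:

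| Route | Limit | Clock starts at |
|---|---|---|
| SAE form (10.3) | 24 hours | knowledge of the event |
| CRF (10.2) | 2 weeks = 14 days | completion of the page |
| CRF (11.2) | 4 weeks = 28 days | the visit |

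Assume, for illustration, that knowledge, completion and visit fall on the same day. The CRF route is then later by up to 14 − 1 = 13 days under Section 10.2, or 28 − 1 = 27 days under Section 11.2. If the page is completed later, or the event falls between visits, the delay is longer. Section 10.2 sets no limit on when the page must be completed.

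**8. How much of chemotherapy is covered by NMES?** Section 9.6 marks daily use from week 2 to week 9, or to week 12 with a fourth cycle. That is 9 − 2 + 1 = 8 of 9 weeks (89%), or 12 − 2 + 1 = 11 of 12 weeks (92%). Section 12.3 plans 26 participants in the NMES arm. Most chemotherapy-period admissions in that arm would therefore fall within device use, but the protocol gives no admission rate, so no count follows.

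**The case against.** The strongest reply is that the exemption changes timing and form, not assessment. That stands. A reader might infer that NMES-related serious harm goes unassessed, drops off the six-monthly list, or lets the trial report no NMES-related SAEs because of the rule itself. The documents do not support this. Sections 10.3 and 10.4 require causality assessment by site and centre, and Section 10.4 states "The WCTU will report a list of all SARs (expected and unexpected) and any other safety recommendations to all PIs every six months", with no exclusion for events that came by CRF. An event would be missing from that list only if it were misclassified.

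Second, the exemption is defined by cause: infection is an example of a chemotherapy toxicity, so an infection attributed to the electrode site remains immediately reportable. This is fair for a clear-cut case. It does not settle an event with two possible contributors, and the extension to SARs in Section 10.3 points the other way.

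Third, a specific exception may be read as qualifying the general real-time statements. That reading is possible, but neither Section 9.6 nor Section 12.2.2 refers to an exception, so the reader has to supply the link. The wording in Section 10.0 about a link that cannot be excluded defines a device-related event; it sets no reporting time, and it is not counted here as a contradiction.

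Fourth, there are other safeguards: scheduled toxicity checks, weekly calls, IDMC safety review and a randomised control arm. They help. However, a comparison of admissions between 26 and 21 participants is a weak check and cannot identify a single device-related event.

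Finally, a PI who overlooks the device would also grade the event as unrelated. True: the fix makes that judgement explicit and recorded but cannot make it correct.

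**Conclusion.** The point holds as a matter of delay and possible misattribution. Followed as written, Sections 10.2 and 10.3 allow a serious event possibly related to NMES to bypass the 24-hour form because of the label given to it. It can then arrive some two to four weeks later or more, on a page for which no causality grade is stated as required. The two CRF return times also disagree, so the length of the delay is not fixed.

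This is a modest fault with a cheap remedy. It does not affect the primary endpoint or sample size. How many events it would touch is unknown. The conclusion assumes that the CRF page has no required causality field and that the Section 10.5 flowchart does not already separate out possibly NMES-related events; neither the CRF nor the flowchart was available to check. If both already do so, what remains is the SAE/SAR wording, the conflicting return times and the unqualified real-time statements.

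**What to change.** Reconcile Sections 9.6 (note), 10.2, 10.3, 11.2 and 12.2.2:

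- In Section 10.2, limit the reporting exemption to listed events that the PI has recorded as unlikely or not related to NMES. Events graded possibly, probably or definitely related then follow the existing 24-hour route.
- In Section 10.3, remove SAR from the exemption.
- Put the existing five-level NMES causality grade on the CRF page used for exempt SAEs, if it is not already there.
- State one CRF return time, used in both Section 10.2 and Section 11.2.
- In Sections 9.6 and 12.2.2, refer to the exemption so that the real-time statements match it.

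The cost is a short amendment, at most one added CRF field, and a few more SAE forms for the site and trials unit. No treatment, endpoint or sample size changes.

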### 10.3 Centre responsibilities

All SAEs must be reported immediately by the PI at the participating centre to the WCTU and the Chief Investigator unless the SAE/SAR is specified as not requiring immediate reporting (see above). All other AEs should be reported on the CRF as usual. The PI should assess the SAE to determine the likely causality with the trial treatment (graded as definitely, probably, possibly, unlikely or not related) and the expectedness (unexpected or expected). A completed SAE form for all events requiring immediate reporting should be faxed to the WCTU and University of Nottingham within 24 hours of knowledge of the event. A separate form must be used to report each event.

**SAE [contact]**

It is also required that sites respond to and clarify any queries raised on any reported SAEs and report any additional information as and when it becomes available through to the resolution of the event.

Serious adverse events should continue to be reported until 30 days after the last patient receives their last dose of the investigational medicinal product. Serious adverse reactions must continue to be reported until the end of follow up.

### 10.4 The Wales Cancer Trials Unit responsibilities

Following the initial report all SAEs should be followed up to resolution wherever possible and further information may be requested by the WCTU. The participant will be identified only by trial number, date of birth and initials. The participant's name should not be used on any correspondence.

WCTU has been delegated responsibility for reporting AEs and SAEs to the regulatory authorities (and relevant ethics committees) as follows:

- A list of all AEs (expected and unexpected) will be reported annually to the Main REC and the trial sponsor.
- The WCTU will report a list of all SARs (expected and unexpected) and any other safety recommendations to all PIs every six months throughout the course of the trial. This frequency may be reviewed and amended as necessary.

Once an SAE or AE is received at the WCTU, it will be evaluated by staff at the WCTU and the Chief Investigator (or their delegate) for seriousness, expectedness and causality.

The causality and expectedness assessment given by the PI cannot be overruled by the CI (or their delegate) and in the case of disagreement, both opinions will be provided with the report. SAEs will be handled at the highest level of event categorisation. This ensures that all SAEs will be reported correctly and included into any Annual / Investigator Safety Reports.

## 10.5 Flowchart for Serious Adverse Event reporting

[figure not shown]

**CRF** Case Report Form  
**SAE** Serious Adverse Event  
**WCTU** Wales Cancer Trials Unit

## **11.0 Trial conduct and monitoring**

### **11.1 Monitoring and quality assurance**

Investigators agree to allow trial related monitoring, including audits and regulatory inspections, by providing direct access to source data/documents as required. Patient consent for this will be obtained.

The conduct of the trial is being overseen by the following committees:

1. An independent Trial Steering Committee (TSC) should meet at least annually and consider each report of the Independent Data Monitoring Committee (IDMC), as well as results of other trials and new information which has arisen, and recommend appropriate action.
2. The Trial Management Group (TMG) should meet at least once every six months to advise in the promotion and running of the trial. The TMG members include active trial investigators, WCTU representatives, Chief Investigators and specialist advisors (e.g. Health Services research and qualitative research advisors, Statistician, consumer representative and oncology representative). Minutes of the TMG meetings will be forwarded to the sponsor as the decisions based on these meetings may impact on the sponsorship arrangements.

### **11.2 Central monitoring**

The top copy of each completed CRF should be returned to the WCTU for data entry within four weeks of the visit. The remaining copy is to be retained at the local centre.

CRF pages and data received by the WCTU from participating trial centres will be checked for missing, illegible or unusual values (range checks) and consistency over time.

If missing or questionable data are identified, a data query will be raised on a data clarification form. The data clarification form will be sent to the relevant participating site. The site shall be requested to answer the data query or correct data on the data clarification form. The case report form pages should not be altered.

All answered data queries and corrections should be signed off and dated by a delegated member of staff at the relevant participating site. The completed data clarification form should be returned to the WCTU and a copy retained at the site along with the participants case report forms.

The WCTU shall send reminders for any overdue data. It is a centre's responsibility to submit complete and accurate data in timely manner.

The University of Nottingham reserves the right to a Sponsor's designee having access to trial data for purposes of review at any time.

### **11.3 Participant withdrawal**

In consenting to the trial, participants are consenting to NMES, trial follow up and data collection. If a participant wishes to withdraw from trial treatment, participating centres should nevertheless explain the importance of remaining on trial follow up for the purposes of data capture only. If the participant explicitly states their wish not to contribute further data to the trial, the WCTU should be informed. A completed withdrawal CRF should be faxed to the WCTU with the hard copy to follow soon after. Participants do not have to give a reason for their withdrawal but centres should make a reasonable attempt to find out why.

Participants should be withdrawn from the trial if they experience any of the following:

- Inability to tolerate electrodes and/or NMES
- Cessation of chemotherapy after 1 or 2 cycles

- Development of a complication that would preclude the use of NMES

Following withdrawal, no further clinical or non-clinical interventions or procedures would be carried out on the participant under the study protocol. No new samples or personal data would be collected. Data already collected in relation to the participant may be retained and used for the purposes for which consent has already been given, provided they are effectively anonymised and no longer identifiable to the research team or any other persons to whom access will be given.

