### 12.3 Sample size calculation

This trial is powered as a Fleming's single stage phase II trial of the intervention arm. The main endpoint is the proportion of patients completing a pre-determined level of compliance to the recommended NMES programme (NMES for 30min three times a week) measured using a self-report daily diary. Following advice from the cachexia subgroup of the NCRI Palliative Care Clinical Studies Group we have determined that 80% of patients should adhere to this minimum level in order to warrant a future phase III study. Conversely, if  $\leq 50\%$  adhered to this minimum level, this would give grounds to reject further study. Using a Fleming's one stage method, 20 patients will be required to distinguish between these rates (90% power,  $p=0.05$ ) and if  $\geq 15$  out of 20 patients adhere, this would warrant further investigation.

We have included a randomised control arm into this trial design in order to allow comparison of some secondary end points. Originally the trial started by randomising with a 1:1 allocation; however this was changed to a 2:1 in favour of the NMES arm allocation part way through the trial in order to support recruitment. As the study analysis is based on a within-intervention arm analysis, the statistical integrity of the study is not affected. A local audit suggests about 25% of patients drop out before reaching 3 cycles. We

require 20 patients in the treatment arm to be available for analysis; therefore we estimate that 26 patients need to be recruited to this arm. At the time of the change in the randomisation allocation ratio this meant that 47 patients would need to be recruited in total (26 to the treatment arm and 21 to the control arm).

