## **12.5 Statistical analyses**

A full statistical analysis plan will be developed before the first interim analysis of the trial data.

For the primary endpoint, the proportion (and 90% confidence interval) of patients completing NMES for 30min three times a week will be reported.

For the secondary (intention to treat) analyses, change in leg muscle strength from baseline will be compared between trial arms at 9, 17 and 20 weeks.

Descriptive statistics will then be presented for the following measures at 9, 17 and 20 weeks:

- Change in QoL score from baseline
- Change in body composition from baseline
- Change in nutritional intake from baseline
- Change in fatigue from baseline

Response to chemotherapy at 9 and 12 weeks will be described in each trial arm.

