##### Participants:

Purposive sampling will be used. As the focus of IPA is on the lived experience of the individual, studies using this methodology are usually conducted using small patient numbers per homogeneous group. This study will define the research group as patients taking part in the trial.  It is assumed that thematic saturation will be reached after 6-10  interviews. The research physiotherapist will approach patients at week 9 or 12 assessments and invite them to take part in this sub-study. All patients are eligible for this sub-study until the qualitative researchers judge that thematic saturation has been reached when the sub-study will be closed. The patient contact details will then be passed to the qualitative researcher in order to arrange interview appointments. Interested patients will be consented and interviewed in clinic or their own home.

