Patient's consent will be sought to notify their GP of their involvement in the trial. Patients should be given sufficient time after being given the trial Participant Information Sheet to consider and discuss participation in the trial with friends and family. A contact number should be given to the patient should they wish to discuss any aspect of the trial. Following this, the randomising investigator should determine that the patient is fully informed of the trial and their participation, in accordance with the principles of ICH-GCP. Patients should always be asked to sign a consent form. One copy should be given to the participant but the original copy should be kept in the study site file and a further copy should be kept with participant's hospital notes.

The right of the participant to refuse to participate in the trial without giving reasons must be respected. After the patient has entered the trial, the investigator must remain free to give alternative treatment to that specified in the protocol, at any stage, if he/she feels it to be in the best interest of the participant. However, the reason for doing so should be recorded and the participant will remain within the trial for the purpose of follow up and data analysis according to the treatment option to which he/she has been allocated. Similarly, the participant must remain free to withdraw at any time from the protocol treatment without giving reasons and without prejudicing his/her further treatment.

This is a randomised trial, therefore neither the participants nor their physicians will be able to choose the patient's treatment. Treatment will be allocated randomly using a computer-based algorithm. This is to ensure that the groups of participants receiving each of the different treatments are similar.

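### Section 11.3 ends data collection for participants who cannot tolerate NMES, which conflicts with the follow-up and intention-to-treat provisions and leaves the primary denominator unsettled

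*Protocol*

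**What the plan says.** Section 11.3 of the protocol contains two different rules. Its first paragraph covers a participant who chooses to stop trial treatment: the centre is to explain why staying on follow-up matters, purely for data capture. Its second part is mandatory: "Participants should be withdrawn from the trial if they experience any of the following". The first item listed is "Inability to tolerate electrodes and/or NMES"; the second is "Cessation of chemotherapy after 1 or 2 cycles"; the third is a complication that would rule out NMES. The consequence is then spelled out: "Following withdrawal, no further clinical or non-clinical interventions or procedures would be carried out on the participant under the study protocol". Collection of anything new from the participant ceases too, although data already held may be kept and used.

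Other sections bear on this:

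- Section 15.1: if the investigator gives alternative treatment, "the participant will remain within the trial for the purpose of follow up and data analysis", with analysis by allocated arm.
- Section 12.5, covering weeks 9, 17 and 20: "For the secondary (intention to treat) analyses, change in leg muscle strength from baseline will be compared between trial arms".
- Section 12.2.1: compliance requires three full sessions in each week of chemotherapy, and missing diary data count as non-compliance.
- Section 12.3: a local audit suggests that about 25% drop out before three cycles. The investigators "require 20 patients in the treatment arm to be available for analysis", so 26 are recruited to that arm, and the pass mark is at least 15 of 20.
- Section 13.0 (Participants): "The research physiotherapist will approach patients at week 9 or 12 assessments" to invite them to interview.

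**The concern.** The trial asks whether NMES is acceptable and feasible during chemotherapy. A participant who cannot tolerate the device is an informative negative answer, yet Section 11.3 stops observing that participant.

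Two things are at stake. The first is the strength comparison between arms. Outcomes that the protocol forbids collecting cannot be recovered by any later analysis, and intolerance can arise in one arm only. The second is the go/no-go decision. It rests on about 20 people, so whether a few intolerant participants count as failures or drop out of the denominator can decide the result. The trial is open, so a denominator left unsettled could be chosen with the results in view.

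**Working it through.** **1. The follow-up provisions side by side**

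| Event | Provision | Follow-up data afterwards |
|---|---|---|
| Participant chooses to stop NMES | 11.3, first paragraph | Encouraged to continue |
| Investigator gives alternative treatment | 15.1 | Continue, analysed as allocated |
| Cannot tolerate NMES, or complication precludes it | 11.3, list | None |
| Chemotherapy stopped after 1 or 2 cycles | 11.3, list | None |

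The triggers overlap in practice. A participant who finds the electrodes intolerable may ask to stop (row 1) or be judged unable to tolerate them (row 3), with opposite consequences for data. Rows 3 and 4 also remove the week 9 and week 17/20 strength measurements on which Section 12.5 relies. Row 4 can occur in both arms. Intolerance occurs only in the NMES arm.

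**2. The primary denominator**

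- Section 12.2.1 implies inclusion: after withdrawal the diary is missing, and missing counts as non-compliant.
- Section 11.3 read with Section 12.3 can imply exclusion: withdrawn participants are arguably not among the 20 available for analysis out of 26.
- The 25% allowance in Section 12.3 concerns only failure to reach three cycles. It is not an intolerance rate.

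**3. The plan's own figures**

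Inputs from Section 12.3: p0 = 0.50, p1 = 0.80, significance level 0.05 (taken as one-sided), power 0.90.

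n = [(1.645 × √(0.5 × 0.5) + 1.282 × √(0.8 × 0.2)) / 0.3]² = [(0.8225 + 0.5128) / 0.3]² = 19.8, so 20, as stated.

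Drop-out: 20 / 0.75 = 26.7, against 26 stated.

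Pass mark: P(X ≥ 15 | n = 20, p = 0.5) = 0.0207. The exact power at p = 0.8 is 0.80 rather than 0.90, which is a separate matter.

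**4. What the denominator could do to a borderline result**

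The number of intolerant participants is assumed, because the protocol gives none. Each is returned as non-adherent. The p-value is P(X ≥ 15 | n, 0.5), and the lower limit is from the 90% Clopper-Pearson interval.

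| Returned | Result | Adherence | One-sided p | Lower limit |
|---|---|---|---|---|
| 0 | 15/20 | 75.0% | 0.021 | 54.4% |
| 1 | 15/21 | 71.4% | 0.039 | 51.3% |
| 2 | 15/22 | 68.2% | 0.067 | 48.5% |
| 4 | 15/24 | 62.5% | 0.154 | 43.7% |

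One returned participant leaves 50% excluded. Two do not.

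**5. False-go probability under exclusion**

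Suppose that true adherence over everyone who should count is 50%, a fraction q is intolerant (all non-adherent) and excluded, and 20 are still analysed. Adherence among those left is 0.5 / (1 − q).

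| Assumed q | 0.5 / (1 − q) | P(X ≥ 15 of 20) |
|---|---|---|
| 0 | 0.500 | 2.1% |
| 5% | 0.526 | 3.5% |
| 10% | 0.556 | 6.1% |
| 15% | 0.588 | 10.5% |
| 20% | 0.625 | 17.9% |

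The condition that 20 are analysed matters. With 26 recruited and 25% lost before three cycles, 19.5 remain. Removing a further 10%, 15% or 20% leaves 17.6, 16.6 or 15.6, that is about 18, 17 or 16. If 15 adherent were still demanded, the false-go probabilities would be 1.3%, 1.0% and 0.6%. The inflation therefore appears only if recruitment continues to 20 analysable patients or the pass mark is rescaled.

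**The case against.** A reader might infer that intolerant participants are removed from the primary denominator and that the adherence estimate is therefore biased upwards. The documents do not support that as a statement of fact. No section says that they are removed. Section 12.2.1 would score them as failures, and Section 11.3 lets data already collected be used. Section 12.3 ties its allowance to not reaching three cycles, which is compatible with intolerant participants being among the 20. Exact analysis sets are also commonly left to the statistical analysis plan. This part of the objection stands: the denominator is in conflict, not shown to be biased.

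The illustrations have limits too. With 26 recruited, 15/24 would require only 2 of 26 (8%) to be lost for other reasons, against the planned 25%. The protocol also sets no pass mark for 22 or 24.

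It would go too far to say that the intention-to-treat comparison becomes impossible. Baseline and pre-withdrawal data remain, the result is missing data in a secondary comparison, and losses from stopping chemotherapy can occur in both arms. Nor do the interviews miss everyone who gave up NMES: those who choose to stop are encouraged to stay in follow-up and can be approached, and Section 13.0 makes all patients eligible. Only those withdrawn under the list are missed. Section 15.1 concerns a change made by the investigator, so its conflict with Section 11.3 is for a related trigger, not the identical one.

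The instruction not to collect data survives the objection. An analysis plan can handle missing values, but it cannot supply measurements that the protocol says not to take.

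**Conclusion.** The point holds as a conflict between provisions. Followed as written, the list in Section 11.3 ends follow-up for reasons that include one specific to the NMES arm. That is inconsistent with the first paragraph of Section 11.3, with the principle in Section 15.1 and with the intention-to-treat comparison in Section 12.5. The week 9 and week 17/20 strength data are exposed to differential loss. How much is lost cannot be stated, because the protocol gives no intolerance rate.

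For the primary endpoint, the conclusion is that Section 12.2.1 and Sections 11.3 with 12.3 give different answers. If exclusion were the practice, as few as two intolerant participants could separate a passing 15/20 from a result that no longer excludes 50%. The false-go probability could rise from 2.1% to between 3.5% and 17.9% for assumed exclusions of 5% to 20%, provided that 20 are still analysed. If Section 12.2.1 governs, neither effect arises.

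**What to change.** 1. Reconcile Section 11.3 with Sections 12.5 and 15.1, so that the listed events may end NMES but do not end data collection. Scheduled assessments continue unless the participant withdraws consent for data. The clinical criteria for stopping NMES stay as they are. Section 9.6 ties assessment timing to treatment cycles, so say when the visits fall for someone who stops chemotherapy early.
2. In Sections 12.3 and 12.5, state that NMES-arm participants who stop for intolerance or an NMES-precluding complication stay in the primary denominator as non-adherent, under Section 12.2.1. State separately how those with fewer than three cycles are handled, since the primary objective refers to patients having at least three. Add a sensitivity analysis over all allocated to NMES.
3. Restate the pass mark if the denominator is not 20. For example, at least 18 of 26 has exact one-sided alpha 0.038 at 50% and power 0.94 at 80%.
4. Offer the interview to those who stopped NMES early.

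The cost is protocol and analysis-plan wording, plus already scheduled visits for a few more participants. The adherence figure may come out lower, and some participants will still decline follow-up.
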